#### • Group 3: Control Subjects

##### Inclusion criteria

Fifty age and gender matched subjects will be included if they have no history of significant neck, scapular or shoulder pain over the past 12 months (significant pain is defined as pain ≥ 3/10 on a visual analogue scale [31,41] and do not use desktop equipment for more than 40% of their working week [24]. The control group will be recruited from staff/students at University College Dublin, St Vincent's University Hospital staff and the local community.

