**Methods/Design:**

Three groups of participants will be investigated: Groups 1 and 2 will be office workers with either NSAP or cervical radiculopathy and Group 3 will be a control group of non office workers without upper limb pain. Participants will undergo a clinical assessment, pain questionnaires (LANSS, Short Form McGill, DASH and TSK) and quantitative sensory testing comprising thermal detection and pain thresholds, vibration thresholds and pressure pain thresholds.

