## Background

Work related upper limb disorders (WRULD) (often called repetitive strain injury) are a significant public health problem, estimated to constitute 45% of all occupational diseases [1]. Non specific arm pain (NSAP) constitutes a subgroup of WRULD [2-5] and has been defined as diffuse pain in the forearm (which can also involve the neck, arm, wrist and hand) in the absence of evidence of a specific upper limb disorder [2-6].

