### Exclusion criteria for all participants

Subjects will be excluded if they are seeking compensation for their injury or if they have any of the following: bilateral upper limb pain, neurological disorders, generalized musculoskeletal disorders e.g. rheumatoid arthritis or fibromyalgia, a history of low back pain and/or low back related leg pain over the previous 6 months, a history of migraine over the previous 6 months, previous surgery or trauma to the upper quadrant, diabetes or endocrine disorders, epilepsy or any psychiatric disorders. Participants taking anti-epileptic or anti-depressant medication, or who are undergoing chemotherapy/radiotherapy will also be excluded.

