**Figure 1 F1:**
[figure not shown]
**Study Protocol**.

All other participants will be screened by means of a subjective examination, pain area mapping and a clinical orthopaedic examination to identify participants with NSAP and to exclude patients with all other specific upper limb disorders according to classification criteria outlined by Boocock et al, [2]. The classification criteria for NSAP are listed in Table 1, with classification criteria for specific upper limb disorders listed in Additional file 1.

**Table 1 T1:** Classification criteria for NSAP

*DEFINITION NSAP*	*SYMPTOMS*	*SIGNS*
Pain in the arm in the absence of a specific diagnosis or pathology	Pain in the forearm and failure to meet the diagnostic criteria of specific disorders *Symptoms may include:* Loss of function Weakness in arms and hands Cramp Muscle tenderness Allodynia Slowing of fine movements Clumsiness	Absence of signs of a specific pathology that correlates with area of pain.

Boocock et al., 2009

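### The control criterion covers only neck, scapular and shoulder pain, so no visible rule excludes a control with unilateral non-specific arm, forearm, wrist or hand pain, although the article calls the controls asymptomatic

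*Protocol article*

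**What the plan says.** The article describes the control group in several places.

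- **Abstract, Methods/Design:** "Group 3 will be a control group of non office workers without upper limb pain".
- **Background (closing paragraph) and Objectives:** the comparison group is called asymptomatic.
- **Group 3: Control Subjects, Inclusion criteria:** controls must have "no history of significant neck, scapular or shoulder pain over the past 12 months", where "significant pain is defined as pain ≥ 3/10 on a visual analogue scale". They must also be people who "do not use desktop equipment for more than 40% of their working week".
- **Exclusion criteria for all participants:** the only entry on upper limb pain as such is "bilateral upper limb pain". Previous surgery or trauma to the upper quadrant is also excluded.
- **Screening and Allocation to study groups:** everyone outside the radiculopathy group has a subjective examination, pain mapping and an orthopaedic examination. The stated aims are to find NSAP and to rule out specific upper limb disorders.

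The cases are defined by pain further down the limb. Table 1 gives the NSAP symptom criterion as "Pain in the forearm and failure to meet the diagnostic criteria of specific disorders", and the Background describes the condition as "diffuse pain in the forearm (which can also involve the neck, arm, wrist and hand").

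**The concern.** The criterion that decides who enters Group 3 names three regions, none of them below the shoulder. The symptom that makes someone a case is located in the forearm. Two of the article's general descriptions of the controls promise more than the criterion delivers.

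The gap lies where the outcomes are measured. Thermal and vibration thresholds are taken on the hand. Pressure pain thresholds are taken over the median, ulnar and radial nerves at the elbow and upper arm. A control with pain in that region may have altered thresholds there. If those thresholds resemble the NSAP pattern, the control mean moves toward the NSAP mean, the control variance grows, and the NSAP-control contrast shrinks. That contrast is part of a stated objective, and analysis cannot readily restore it once such people have been recruited as controls.

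**Working it through.** **Step 1: follow one volunteer through the written rules.** Take a person who is not an office worker and has current unilateral, non-specific forearm pain, with no neck, scapular or shoulder pain.

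| Rule | Result for this volunteer |
|---|---|
| Group 3 pain criterion (neck, scapular, shoulder; 12 months; 3/10) | Met: forearm not listed |
| Group 3 desktop use, not above 40% of the week | Met |
| Common exclusion for upper limb pain | Not triggered: pain is unilateral |
| Common exclusion for upper-quadrant surgery or trauma | Not triggered |
| Screening to exclude specific upper limb disorders | Not triggered: pain is non-specific |
| Groups 1 and 2 office-work criteria (more than 40% desktop use, two years in such work) | Not met, so the person cannot become an NSAP case |

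The volunteer satisfies every visible Group 3 criterion. The common exclusion list could not close the gap by dropping the word bilateral, because both patient groups are required to have unilateral upper limb pain. The protection has to sit in the control criterion.

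**Step 2: compare with the stated control group.** The same volunteer is not without upper limb pain (abstract) and is not asymptomatic (Background, Objectives). The descriptions and the criterion disagree.

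**Step 3: illustrate the effect.** No figure in the article depends on this point, so there is none to reproduce. The article gives 50 per group, an effect size of 0.5 and a two-tailed 0.05 level. The share c of affected controls is assumed, as is that each carries the full NSAP shift.

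- Diluted difference: d(c) = 0.5 × (1 − c).
- Control variance as a mixture: 1 + c(1 − c) × 0.5², averaged with an NSAP variance of 1 to give s²(c) = [2 + 0.25 c(1 − c)] / 2.
- Power (normal approximation): Φ( d(c) × √(50/2) / s(c) − 1.96 ).

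| c (assumed) | d(c) | s²(c) | Power at 50 per group | n per group for 80% power |
|---|---|---|---|---|
| 0 | 0.500 | 1.0000 | 0.705 | 63 |
| 5% | 0.475 | 1.0059 | 0.658 | 70 |
| 10% | 0.450 | 1.0113 | 0.609 | 79 |
| 20% | 0.400 | 1.0200 | 0.508 | 101 |

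For example, at c = 10%: 0.45 × 5 / √1.0113 − 1.96 = 0.28, and Φ(0.28) is about 0.61. A t-test calculation gives 0.697 with no affected controls.

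The starting value lies below the 0.8 in the sample size section. That is a separate matter and is not caused by the control criterion; only the fall down the column belongs to this point.

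**Step 4: the radiculopathy-control contrast.** If affected controls carry an NSAP shift δN and radiculopathy patients a shift δR, the contrast becomes δR − c·δN. The factor (1 − c) would apply only if the two shifts were equal, and the article gives no basis for that.

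**The case against.** The strongest reply is that the intent is clear. The abstract, the Background and the Objectives all point to symptom-free controls, so the region list may simply be incomplete. Pain mapping and examination, on a natural reading, apply to prospective controls too. They would reveal distal pain and remove anyone with a specific disorder. Figure 1, which shows the study flow, is not visible, and an article condenses a fuller protocol.

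Much of this stands, and it limits the point. A reader might infer that the design means to admit symptomatic controls, or that anyone with arm pain could enter. The documents support neither: the stated intent is the opposite, and specific disorders, bilateral pain and prior trauma or surgery are all screened out. What is left is unilateral, non-specific pain that screening may detect but that no visible rule makes a reason to exclude. Nor is this a detail left to a longer document, because the article states the criterion in full, with regions, threshold and look-back.

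A reader might also take the power figures as an estimate of the harm. They are not. The article gives no prevalence of distal arm pain in controls, and screening may keep it low. Whether NSAP shifts these thresholds is itself the study question: the Background reports conflicting vibration findings and says pressure and thermal testing have not been specifically studied in NSAP. A smaller shift in affected controls would dilute the contrast less.

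**Conclusion.** The point holds as a contradiction between the described control group and the criterion that selects it. Read literally, the visible rules admit a non-office-worker control with unilateral, non-specific arm, forearm, wrist or hand pain of any intensity, which includes the defining symptom of the cases.

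The direction of bias, toward no NSAP-control difference at the hand and arm-nerve sites, follows if affected controls have NSAP-like thresholds. The size cannot be established from the documents; the illustrated falls in power, to 0.61 at 10% and 0.51 at 20%, rest on assumed shares and a full case-size shift. No figure is supported for the radiculopathy-control contrast. The contradiction itself depends on none of these numbers.

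**What to change.** Reconcile the Group 3 inclusion criterion with the abstract, Background and Objectives. Extend it to pain anywhere in the neck, the scapular region or either upper limb, naming arm, elbow, forearm, wrist and hand.

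State at the same time which standard applies: no pain at or above 3/10, or no upper limb pain at all. Extending the regions while keeping the 3/10 threshold would still admit milder arm pain, which the abstract's description does not. Say also whether the 12-month look-back covers the added regions.

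The cost is one line in the eligibility criteria, a matching line on the screening form, and slightly more controls screened out. The pain mapping already planned would supply information on current pain; a look-back would need a question at interview.

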### QST findings in musculoskeletal disorders

While pressure pain thresholds or thermal QST have not been specifically investigated in NSAP, studies of other working populations have yielded mixed results. Increased sensitivity to pressure has been found in the shoulder and neck muscles of butchers [31], secretaries [32] and manufacturing workers [33]. Contrary to this, Johnston et al., [34] found office workers with neck pain showed no difference in pressure pain thresholds (PPT) over the neck muscles in comparison to controls but they did have lower PPT at median nerve and tibialis anterior sites. Increased sensitivity to pressure has also been found in whiplash and cervical radiculopathy patients [35,36]. In relation to thermal QST, Johnston et al., [34] found that office workers with mild neck pain and disability had decreased heat pain thresholds and were more sensitive to cold pain than controls or office workers without pain. Furthermore, alterations in thermal detection thresholds have been found in the upper limbs of patients with whiplash and cervical radiculopathy [37]. One interesting finding in this study by Chien et al. is the presence of non-symptomatic to symptomatic side differences in the cervical radiculopathy group which did not exist in the whiplash group. Whilst further investigations are warranted to elucidate the significance of this finding, it may reflect a difference between neuropathic versus non-neuropathic pain presentations.

Recent investigations into work related neck pain [34]; diffuse upper limb pain [28], low back pain [38], whiplash [20,36], patellofemoral pain syndrome [39], fibromyalgia and complex regional pain syndrome [40] have shown that these conditions may have a neuropathic pain component. However, many of these studies show positive findings on both the asymptomatic and symptomatic sides, indicating that change may just be reflective of alterations in somatosensory processing associated with pain i.e. central plasticity from nociceptive or inflammatory pain as opposed to true neuropathic pain [14].

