Clearly, there is much debate as to whether NSAP, which appears to have features of neuropathic pain, is indeed a neuropathic disorder. Furthermore, there are currently no gold standards with which to classify pain as definitively neuropathic. The purpose of this study is to comprehensively describe the somatosensory profiles in patients with NSAP and to compare them to somatosensory profiles in asymptomatic subjects and subjects with cervical radiculopathy. It is hypothesised that some of the NSAP group may demonstrate a similar presentation to that of cervical radiculopathy, indicating a probable neuropathic pain presentation.

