## Methods/Design

### Objectives

The objectives of this study are to:

• Describe the somatosensory profiles of subjects with NSAP in terms of neurological examination, qualitative measures of pain, neural tissue provocation tests and QST.

• Describe impairment and disability associated with NSAP by means of the Disabilities of the Arm, Shoulder and Hand (DASH) and SF-36 questionnaires.

• Investigate for correlations between clinical examination findings, QST profiles and questionnaire derived pain profiles in subjects with NSAP.

• Compare somatosensory profiles of subjects with NSAP to those with cervical radiculopathy and asymptomatic controls.

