#### • Groups 1 and 2: NSAP and Cervical Radiculopathy subjects

##### Inclusion criteria

All participants from patient groups will be office workers who have significant unilateral upper limb pain as defined by a numerical rating score of ≥ 3/10 [31,41], who spend more than 40% of their working week using desktop equipment [24] and have been in their current employment or similar (i.e. involving office work/keyboard operation) for at least two years [34]. More specific information regarding diagnostic criteria for each patient group is outlined in the next section. Patients will be recruited from local orthopaedic outpatient and occupational health departments of Dublin hospitals and physiotherapy practices and also from the staff and student population of University College Dublin.

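### The objective calls for asymptomatic controls, but the stated entry rule for Group 3 sets no limit on current pain below 3/10 and names no site below the shoulder

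*Protocol article*

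**What the plan says.** The protocol article describes the control group in three places as free of pain, and defines it in a fourth by a threshold.

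- **Abstract, Methods/Design:** "Group 3 will be a control group of non office workers without upper limb pain".
- **End of the Background (purpose of the study):** the NSAP profiles are described in order to "compare them to somatosensory profiles in asymptomatic subjects and subjects with cervical radiculopathy".
- **Objectives, last item:** "Compare somatosensory profiles of subjects with NSAP to those with cervical radiculopathy and asymptomatic controls".
- **Group 3: Control Subjects, Inclusion criteria:** controls must have "no history of significant neck, scapular or shoulder pain over the past 12 months", and "significant pain is defined as pain ≥ 3/10 on a visual analogue scale". Limited use of desktop equipment is the other condition.

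Three further sections bear on who can enter. The exclusion criteria for all participants list "bilateral upper limb pain, neurological disorders, generalized musculoskeletal disorders" among others. The section on screening and allocation sends everyone outside the radiculopathy route through a subjective examination, pain mapping and an orthopaedic examination; its stated purpose is to find NSAP and to exclude specific upper limb disorders. The Pain Assessment section gives the detailed assessment of pain intensity and quality to the two patient groups only.

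**The concern.** A cut-off of 3/10 is a reasonable way to say that a past episode of pain was significant. Its complement is not the same thing as being asymptomatic. A volunteer with current one-sided neck or shoulder pain of 1/10 or 2/10 satisfies the Group 3 rule and would be analysed as an asymptomatic control.

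The rule also omits the body region that matters most here. Table 1 defines NSAP by forearm pain, yet the control rule mentions only neck, scapula and shoulder.

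The article's own Background gives a reason to care. It reports a study in which "office workers with mild neck pain and disability had decreased heat pain thresholds and were more sensitive to cold pain than controls". Heat and cold pain thresholds are outcomes of this study. If mildly painful controls carry part of the sensory change seen in patients, the control mean moves toward the patient means and the differences shrink. A finding of no difference between NSAP and Group 3 could then not be read as no difference from asymptomatic people, which is what the objective asks. Because no control pain score is planned in the visible text, the problem could not be measured or adjusted for afterwards.

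**Working it through.** **Step 1. Does any visible rule close the gap?** Take a volunteer with current one-sided pain below 3/10.

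| Section | Effect on this volunteer |
|---|---|
| Group 3 inclusion criteria | Admitted: neck, scapular or shoulder pain is below the cut-off; pain lower in the arm is not named |
| Exclusion criteria for all participants | Removed only if the upper limb pain is bilateral |
| Screening and Allocation | Pain is mapped, but the stated aim is to identify NSAP and specific disorders; no pain-free requirement for controls is stated |
| Pain Assessment | Does not apply: patient groups only |

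Nothing visible requires the volunteer to be pain-free, although the abstract, the purpose statement and the objective describe Group 3 that way.

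**Step 2. The plan's own figure.** The Sample size/power calculation section gives 50 per group, effect size 0.5, power 0.8 and a two-tailed 0.05 level. For a two-sample t-test the noncentrality is d × √(n/2) = 0.5 × √25 = 2.5, with 98 degrees of freedom and critical value 1.984. Power is 0.697, and 0.8 would need 64 per group. The stated 0.8 is therefore not reproduced. That is a separate matter and lends no weight to this point; 0.697 serves only as the baseline below.

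**Step 3. Dilution under assumptions.** Let q be the share of controls with pain below the cut-off, and f the fraction of the patient-control difference that they carry. Neither is in the document; both are assumed. The expected observed effect is

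d = 0.5 × (1 − q × f).

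| q | f | d | Power, 50 per group | Loss (points) |
|---|---|---|---|---|
| any | 0 | 0.500 | 0.697 | 0 |
| 0.05 | 0.25 | 0.494 | 0.686 | 1 |
| 0.20 | 0.25 | 0.475 | 0.652 | 4 to 5 |
| 0.20 | 0.50 | 0.450 | 0.606 | 9 |
| 0.30 | 0.50 | 0.425 | 0.557 | 14 |

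A loss of 5 points is reached at d = 0.472, that is q × f = 1 − 0.472/0.5 = 0.056: for example, 11% of controls carrying half the effect. Allowing for the extra spread that a mixed control group introduces lowers these powers by at most 0.003. A more extreme assumption gives a larger loss (q = 0.5 and f = 0.5 gives d = 0.375 and power 0.46), but nothing in the document suggests that half the controls would have mild pain.

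**The case against.** **The cut-off may govern history only.** The 3/10 rule looks back over 12 months, and a threshold suits such a look-back, since minor aches are common and poorly recalled. On this reading current status is settled by the words asymptomatic and pain-free elsewhere in the article. The reading is fair, but it still leaves no operative criterion for current pain: those words stand in the abstract, the purpose and the objective, not in the entry rules.

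**Screening may catch such people.** Pain mapping is already planned for everyone outside the radiculopathy route, and Figure 1 is not available here. A rule might appear there. The text that can be read states none.

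**Stronger readings that the document does not support.**

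- A reader might infer that mildly painful controls will enter and will shrink the differences. The rule permits their entry; it does not show that they will come, or how many.
- A reader might infer that a patient and a control can be one point apart on the same scale. Patients need "significant unilateral upper limb pain as defined by a numerical rating score of ≥ 3/10" together with diagnostic criteria, whereas the control rule uses a visual analogue scale, other body sites and a 12-month window. The two cut-offs are not comparable in that way.
- A reader might infer that the Background proves the effect. The cited study concerned office workers with neck pain and disability, while Group 3 is limited in desktop use. Nothing equates mild in that study with 1/10 or 2/10. The same study found lower pressure pain thresholds at the median nerve but no difference over the neck muscles. The Background also says that pressure pain and thermal testing have not been specifically studied in NSAP.
- No section links mild pain to vibration thresholds, the outcome used for sizing.

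The power model is also a two-group t-test, whereas the planned analysis is a one-way ANOVA with Student-Newman-Keuls comparisons. The figures are illustrative.

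**Conclusion.** The mismatch stands. The article names an asymptomatic comparator, but its stated entry rule allows current neck, scapular or shoulder pain below 3/10 and is silent on the rest of the arm. The only visible relief is the exclusion of bilateral upper limb pain. People with mild current pain can enter Group 3, and if they do, patient-control differences may be biased toward zero, most plausibly for heat and cold pain thresholds.

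The size is not derivable from the document. Under the assumed shares and effects above, power falls from about 0.70 by roughly 1 to 14 percentage points; if mild pain carries no sensory effect, nothing is lost. Severity is minor to moderate: the possible bias is uncertain in size, but it touches the meaning of the reference group and is cheap to prevent.

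**What to change.** Keep the 12-month rule and bring the Group 3 inclusion criteria into line with the objective by adding one condition: a control must report no current pain (0/10) in the neck, scapular region and upper limb at testing. The subjective examination and pain map already planned at screening can carry the check. Naming the upper limb also closes the gap for arm, forearm, wrist and hand.

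If controls are already enrolled, record their current pain score and repeat the patient-control comparisons in those scoring 0/10, reported beside the main comparison.

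The cost is one sentence and one screening question. A few volunteers from the pool of university and hospital staff, students and the local community would be turned away or rescheduled. The control group would be slightly healthier than the general population, but that is the reference the objective names.
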